#### - Phase 3: (Post) discharge phase

In the discharge phase, the patient is prepared for living at home and is referred to local physiotherapists, specialised sport clubs and mental health care professionals.

#### Conventional multi-trauma care service

CTCS is provided in several centres. Multi-trauma patients are admitted to hospital via the A&E department. After possible surgery, they are transferred to the IC-unit, followed by the hospital's nursing ward, where the patient may stay for several days or weeks. The trauma surgeon, as chief consultant, decides whether or not a rehabilitation physician will be consulted during hospitalisation. Next, ensuing treatment may take place in the hospital's outpatient clinic, in a rehabilitation centre, in a nursing home or with a local GP or physiotherapist. Van Vree and co-workers ([15]) reported that, typically, each of the CTCS "stages" might have its own more-or-less autonomous treatment perspective, depending on the professional's individual treatment views and experience.

The effectiveness of multi-trauma rehabilitation interventions and its constituting elements has been established in numerous studies. Recently, Holtslag [16], in his PhD research, investigated the long term outcome after major trauma. However, whereas most clinical studies compare single treatment outcome, no randomised clinical trials on treatment effects in multiple trauma patients have been found to date.

### Data collection

Baseline measurements will be administered as soon as possible post-injury (= T0). Further measurements will be taken at 3 months (= T1), 6 months (= T2), 9 months (= T3) and 12 months (= T4) post-trauma (see also flow chart, figure 1).

### Demographic and medical variables

Upon arrival at the A&E (= T0) the following variables will be recorded: age, gender, medical history, mediation usage, diagnosis, ISS score, date and time of trauma and Glasgow Coma Scale (GCS).

As soon as possible post-injury the following data are collected: trauma treatment, possible complications (description, number and extend) and time in hospital. The following additional data are recorded upon admission in the rehabilitation centre: individual rehabilitation treatment aims, pre-trauma psychosocial status and pre-trauma employment status.

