### Statistical analyses

In non-randomised comparative studies, variations in case mix between centres can influence the interpretation of outcome data [48]. Therefore, for each of the data sets collected at T1 through T4, differences in outcome variable between the 2 services will be tested using multiple MANCOVA's, entering various indicators of case mix as co-variates, i.e. age, gender, ISS, number of complications, pre-trauma psycho-social status.

When patients drop out of the study, the reason for their withdrawal will be recorded. Drop-outs may bias the treatment effect evaluations. Therefore, the following regime will be applied:

- Missing T4 measurement: 'last-observation-carried-forward' principle will be applied.

- Missing T3 or T2 measurement: linear interpolation of data using data from adjacent time points (e.g. T1 and T4) for imputation.

- Missing T0 or T1 measurement or more than 2 missing measurements: discarding of patient data and influx of additional patient in order to meet n = 82 per group.

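### Pre-trauma psychosocial status is a model covariate, but its only scheduled recording point is admission to a rehabilitation centre, which some conventional-care patients never reach

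*Protocol article*

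**What the plan says.** Under Demographic and medical variables, the protocol article sorts data by when they are collected. The first list is taken at the emergency department: "Upon arrival at the A&E (= T0) the following variables will be recorded: age, gender, medical history, mediation usage, diagnosis, ISS score", with time of trauma and the Glasgow Coma Scale. The second, taken as soon as possible after injury, covers trauma treatment, complications and hospital time. The third reads: "The following additional data are recorded upon admission in the rehabilitation centre: individual rehabilitation treatment aims, pre-trauma psychosocial status and pre-trauma employment status". Psychosocial status appears in the third list only.

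Under Statistical analyses, "for each of the data sets collected at T1 through T4, differences in outcome variable between the 2 services will be tested using multiple MANCOVA's", and the adjustment is made by "entering various indicators of case mix as co-variates, i.e. age, gender, ISS, number of complications, pre-trauma psycho-social status".

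Under Conventional multi-trauma care service, "ensuing treatment may take place in the hospital's outpatient clinic, in a rehabilitation centre, in a nursing home or with a local GP or physiotherapist". The trauma surgeon "decides whether or not a rehabilitation physician will be consulted during hospitalisation". Under Interventions/services, by contrast, early transfer to a specialised rehabilitation unit is a listed component of SFTRS.

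Table 1 requires a rehabilitation indication, meaning that lasting impairment is expected. It does not require admission to a rehabilitation centre.

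**The concern.** The study is not randomised, so the covariates are its stated protection against differences in case mix. The section on primary outcomes itself says that recovery depends on psychological and social factors, so this covariate matters. Yet whether it is collected depends on a step in the care pathway that comes after injury and differs by design between the two services.

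The gap therefore falls mainly on CTCS. If it decides who is analysed, CTCS patients who reached a rehabilitation centre are compared with an SFTRS group for whom such admission is part of the service. The adjustment variable would then bring in a selection of its own. An analysis plan cannot recover a value that was never collected.

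**Working it through.** **Setting the sections side by side**

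1. The covariate is needed for every analysed patient at T1, T2, T3 and T4 (Statistical analyses).
2. Its only scheduled recording is at rehabilitation-centre admission (Demographic and medical variables).
3. A rehabilitation centre is one of several CTCS destinations (Conventional multi-trauma care service), and eligibility does not require admission to one (Table 1).
4. So eligible CTCS patients treated elsewhere have no scheduled value.

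The listed missing-data rules can then lead two ways. If the item is not counted as a T0 measurement, no listed rule applies, and a MANCOVA run in the usual way omits patients who lack a covariate. If it is counted as one, the patient is discarded and another recruited until n = 82. Both ways, the analysed CTCS group consists of patients who reached a rehabilitation centre.

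**The plan's own figures (Population)**

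- Target difference: 0.15 × 30.2 = 4.53 FIM points; SD 9.5; two-sided 0.05; power 80%.
- n per group = 2 × (1.96 + 0.8416)² × 9.5² / 4.53² = 69.04, rounded up to 70. The t-test version gives 70.01, rounded up to 71, as stated.
- 71 × 1.15 = 81.65, rounded up to 82, as stated.

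**Illustration of a possible shift**

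The document gives neither the share p of CTCS patients not admitted nor the correlation r between mildness and FIM at T1. Both are assumed here. Suppose the mildest share p is lost at a sharp cut-off, every SFTRS patient is retained, and nothing is adjusted. With q the standard normal quantile at 1 − p and φ the normal density, the analysed CTCS mean falls by

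shift = r × 9.5 × φ(q) / (1 − p)

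| p | φ(q)/(1 − p) | r = 0.3 | r = 0.5 |
|---|---|---|---|
| 20% | 0.350 | 1.00 (22% of 4.53) | 1.66 (37%) |
| 40% | 0.644 | 1.84 (41%) | 3.06 (68%) |
| 60% | 0.966 | 2.75 (61%) | 4.59 (101%) |

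Worked cell: p = 40%, r = 0.5 gives 0.5 × 9.5 × 0.644 = 3.06.

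If the milder patients are lost, the shift favours SFTRS. If the more severe are lost, for example to nursing homes, the sign reverses. A blurred cut-off, or covariates that capture mildness, makes the shift smaller.

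**The case against.** Four points on the other side deserve weight.

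*Exclusion is inferred.* A reader might conclude that these patients drop out of every MANCOVA. The article does not say so. It does not say that the item may never be recorded elsewhere, nor that the models use complete cases, and handling of missing covariates may properly sit in an analysis plan that is not shown. This stands, so the absence of an imputation rule is no part of this point. Imputation would not fully close the gap, though: CTCS values would have to be borrowed from CTCS patients who were admitted.

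*Power.* A reader might infer a loss of power. With SFTRS at 71 and CTCS cut by 20%, 40% or 60%, power for 4.53 points would fall from 81% to 76%, 69% or 57% (normal approximation). But the plan recruits further patients to reach 82 per group when a T0 measurement is missing, and expects about 467 patients per region. A loss of power cannot be asserted. Comparability is what remains.

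*Size.* A reader might take the 37% to 101% in the r = 0.5 column as the bias in the trial's result. Those are unadjusted shifts under assumed inputs. The model adjusts for age, gender, ISS and complications. If these carried the whole link between mildness and FIM in a correctly specified linear model, the shift in the adjusted difference would be zero. The rehabilitation indication in Table 1 may also make admission common in CTCS, and no SFTRS transfer rate is stated.

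*Related items.* It is tempting to extend the point to employment status and the COPM. Employment status is not a listed covariate, and production losses are measured with the PRODISQ at baseline and T1 to T4. The section on secondary outcomes already ties the COPM to aims set during rehabilitation. Neither extension holds.

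Finally, pre-trauma status is historical and could be asked later. That shows the gap is easy to close. It does not show that the plan closes it.

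**Conclusion.** The point holds as a mismatch between the recording schedule and the analysis model: a named case-mix covariate has no scheduled collection for CTCS patients treated outside a rehabilitation centre. It rests on three sections of the same article and needs no outside figure. It also rests on reading the third data list as the only recording point, since no other is given.

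The consequence is conditional. If patients without the value are left out, or are discarded and replaced, CTCS is selected on a post-injury event that is part of what is being compared. The direction and size of the resulting bias are unknown. The range of about 1.0 to 4.6 FIM points shows only that the effect could be material beside the planned 4.53. It depends on the assumed shares and correlations, and adjustment for ISS and complications would reduce it.

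**What to change.** Record pre-trauma psychosocial status for every participant in both groups at T0, or at the consent contact where the credibility/expectancy questionnaire is already given, whatever the later care setting. Amend the data list under Demographic and medical variables to match.

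The cost is small: one questionnaire moves to an existing contact, with a minor edit to the protocol and the case report form. Treatment aims can stay where they are, since they belong to the rehabilitation phase.

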### Outcome measures

Outcome measures are presented in table 2.

**Table 2 T2:** Primary and secondary outcome measures

Primary outcome measures	Generic quality of life	SF-36
	Functional health status	FIM
Secondary outcome measures	Anxiety and depression	HADS
	Cognitive functioning	MMSE
	Extent to which individual ADL treatment goals are met	COPM

Note: Costs will be assessed using the PRODISQ, a cost questionnaire and hospital database data		

FIM: Functional Independence Measure; COPM: Canadian Occupational Performance Measure; HADS: Hospital Anxiety and Depression Scale; MMSE: Mini-Mental State Examination; PRODISQ: PROductivity and DISease Questionnaire

### Primary outcome measures

In the current study the primary outcome measures are FIM, measuring quality of life and SF-36, measuring functional health status. In several studies it was found that in multi-trauma patients quality of life and functional recovery do not solely depend on injury severity and complications [6-9], but also on psychological and social factors (e.g. [5,17-20]) as well as the patient's cognitive status [21]. The Functional Independence Measure (FIM) is widely used in assessing functional health status in different groups of patients. Baldry-Currens [22,23] recommended using the FIM in assessing trauma outcome, the FIM correlating high with measures of injury severity and demonstrating clinical and statistical significance. Similarly, Hetherington and co-workers [24,25] reported that in rehabilitation services, the FIM is a useful, practical and simple methodology, providing a measure for assessing the original disability, its progress and residual limitations. The National Trauma Data Bank collects data on trauma centre performance throughout the USA. As to functional outcome assessment in trauma patients FIM data are used [26].

At an international and interdisciplinary consensus conference in 1999 about the assessment and application of quality of life (QoL) measures after multiple trauma, experts clinicians and methodologists agreed on the SF-36 as generic tools for QoL assessment across all trauma patients [27]. In the proposed study both generic QoL and utilities will be derived using the SF-36. An overall utility score for population based QoL can be obtained, which facilitates comparisons with other interventions, i.e. the social tariff of the SF-36 [28-33].

### Secondary outcome measures

The Canadian Occupational Performance Measure (COPM) is an individualised client-oriented measure to assess the evolution of self-perception of skills in patients across time [34,35]. The COPM was, for example, used by Trombly and co-workers [36] to investigate the association between participation in goal-specific outpatient occupational therapy and improvement in self-identified goals in adults with acquired brain injury. In our study the COPM will be used to assess the extent to which individual treatment aims of the multi-trauma patient, set during rehabilitation, are met.

The Hospital Anxiety and Depression Scale (HADS) gives clinically meaningful results as a psychological screening tool, in clinical group comparisons and in correlational studies with several aspects of disease and quality of life. It is sensitive to changes both during the course of diseases and in response to psychotherapeutic and psychopharmacological intervention. Finally, HADS scores predict psychosocial and possibly also physical outcome [37]. The HADS has been used by Kempen and colleagues [38] to investigate the effect of depressive symptoms on the recovery of activities of daily living after fall-related injuries to the extremities in older persons. As stated before, anxiety and depression, among others, may influence therapy outcome in multi-trauma rehabilitation. Therefore, in the present study the HADS is used to assess this aspect. The Mini-Mental State Examination (MMSE) is a test that briefly surveys global mental status in a wide range of cognitive domains [39-41]. Jackson and co-workers [39] used the MMSE in trauma survivors without intracranial haemorrhage. Their findings corroborated earlier research stating that these patients display persistent cognitive impairment associated with functional defects, poor quality of life, and an inability to return to work [39]. In our study the MMSE will be used similarly, i.e. to assess global cognitive functioning of multi-trauma patients.

### Treatment credibility and expectancy

In studies comparing the effectiveness of different treatment regimes, differences in treatment credibility and expectancy may influence the outcome. In the proposed study the credibility/expectancy questionnaire (CEQ) [42] will be administered directly following the explanation of the study's rationale to patients, i.e. after informed consent has been obtained.

### Determination of costs

General considerations:

For the economic evaluation the main research question is:

From the viewpoint of the society is another organisation of professional care service for trauma patients (i.e. SFTRS) compared to CTCS preferable in terms of costs, effects and utilities?

Based on this main research question several sub-questions are relevant:

1) What are the costs of SFTRS compared to CTCS preferable in terms of costs, effects and utilities?

2) What are the extra effects (measured in quality of life, utilities, and saving by reducing inpatient hospital admissions of multi-trauma patient) of SFTRS compared to CTCS preferable in terms of costs, effects and utilities?

We hypothesise that SFTRS is associated with a reduction in health care and patient costs, and an improvement in quality of life, compared to CTCS. We expect SFTRS to be cost-effective from a societal perspective. Assessments of the quality of life and costs will take place at T1 through T4.

In the cost identification, the following costs are considered:

Health care costs: cost of the intervention program and other health care resources both by the patient and the caregiver.

• Patient and family costs: informal care, paid domestic help, transportation, over the counter medication, and other out-of-pocket expenses.

• Production losses: absenteeism, presenteeism (loss of productivity while at work), and compensation mechanisms for both the patient and the caregiver, if relevant.

Measurement of volumes:

• Hours spent on the intervention program will be recorded on a pre-structured form by the acting healthcare professionals.

• All other health care costs and patient & family costs will be recorded in a cost questionnaire.

• Production losses will be measured using the patient modules of the PRODISQ [43,44].

The PRODISQ will be used together with the costs questionnaire, every 3 months at baseline and T1 through T4.

For the valuation of health care costs and patient & family costs, an update of the Dutch manual for costing in economic evaluations [45] will be used. For care for which no costs-guidelines are available estimations of the costs will be made, based on the real costs and/or on population based estimates from literature. Valuation of production losses will be based on a modification of the friction cost method

Both generic Quality of life (QoL) and utilities are derived from the SF-36. An overall utility score for population based QoL can be obtained, which facilitates comparisons with other interventions, i.e. the social tariff of the SF-36 [28-33].

The primary outcome measure for the cost-effectiveness analysis will be FIM. The primary outcomes measure for the cost-utility measure will be utilities based on the SF-36 social tariff.

The time horizon is 12 months. Ratios will be determined, based on incremental costs and effects of SFTRS compared to CTCS. The cost-effectiveness ratio will be stated in terms of costs per improvement on the FIM. The cost-utility ratio will focus on the net cost per QALY gained. Bootstrap re-sampling techniques [46,47] are used to explore cost-effectiveness uncertainty.

Sensitivity analyses will be performed for the costs that turn out to have the largest impact on the differences in total costs between SFTRS and CTCS. In these analyses both the variance in volumes and prices will be considered. The range over which uncertain factors are thought to vary will be assessed by calculating a minimum and maximum (mean value of costs minus or plus the SD).

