## Introduction

In the Netherlands, with a population of approximately 16 million people, every year about 99.000 persons are admitted to hospital after an accident, whereas 880.000 people visit the Accident & Emergency department (A&E) after an accident [1]. These accidents lead to considerable societal costs. Direct medical costs are estimated at 1 billion Euro/year, i.e. 3–4% of the total Dutch health care budget. Production losses due to acute trauma are estimated at 4 billion Euro, thus widely surpassing costs of chronic illness like cardiovascular diseases and cancer [2-4]. Many of the patients have multiple fractures. Major causes of multi-trauma are traffic accidents, accidents at work, (extreme) sports, falls, blasts, etc. [5]. The legs (incl. pelvis) are most frequently injured in multi-trauma [6-9]. Multi-trauma occurs more often in males and in younger adults [5]; [10]. Many patients are at an age where they have a paid job. Furthermore, the rehabilitation of the multi-trauma patients may take a long time. The societal impact of multi-trauma is therefore large.

Medical care for trauma patients is a combined responsibility of hospitals, ambulance services, trauma centres, rehabilitation clinics and GHOR (medical assistance after accidents and disasters). This co-operation between teams of specialists is called 'trauma care chain' (TCC). In the present study multi-trauma is defined as having 2 or more injuries of which at least 1 is life threatening, including trauma with an Injury Severity Scale (ISS) score > = 16; complex multiple injuries on both lower extremities; a combination of 1 upper and 1 lower extremity injury, the latter of which can not be used in load-bearing; or complex pelvis/acetabulum fractures. Several tools for rating trauma severity have been designed [11]. The ISS [12,13] is used most often.

In conventional multi-trauma care service (CTCS) each of the partners has its own more or less autonomous treatment perspective, depending on the professional's individual treatment views and experience. Clinical evidence, however, suggests that an integrated multi-trauma rehabilitation service approach or 'Supported Fast track multi-Trauma Rehabilitation Service' (SFTRS), featuring:

1) Earlier involvement of the rehabilitation physician in the hospital;

2) shorter stay in hospital and earlier transfer of multi-trauma patients to a specialised trauma rehabilitation unit;

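### Production losses count in the societal cost comparison of two regions, but pre-trauma employment enters no stated adjustment, so a true regional difference in the employed share would appear as a cost effect of SFTRS.

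*Protocol article*

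**What the plan says.** All references are to the protocol article.

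- **Costs counted.** Under Determination of costs, one of the three cost categories is "Production losses: absenteeism, presenteeism (loss of productivity while at work), and compensation mechanisms", counted for the patient and, where applicable, the caregiver. On measurement: "Production losses will be measured using the patient modules of the PRODISQ". On valuation: "Valuation of production losses will be based on a modification of the friction cost method".
- **Groups.** Under Population, SFTRS patients come from the southern trauma region and the reference group from another trauma region. Randomisation is ruled out.
- **Employment.** Under Demographic and medical variables: "The following additional data are recorded upon admission in the rehabilitation centre", followed by "individual rehabilitation treatment aims, pre-trauma psychosocial status and pre-trauma employment status". Employment and psychosocial status are two separate items.
- **Adjustment of outcomes.** Statistical analyses acknowledges that case mix may differ between centres. It then names the covariates for the MANCOVAs on the outcome variables: "i.e. age, gender, ISS, number of complications, pre-trauma psycho-social status". Employment is not among them.
- **Cost analysis.** The end of Determination of costs bases the ratios on incremental costs and effects, uses the bootstrap for uncertainty, and varies volumes and prices in sensitivity analyses. It states no covariate adjustment.

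**The concern.** Having paid work before the injury is a precondition for the patient's own absenteeism and presenteeism. It is fixed before either service begins, so a difference between the groups in the employed share cannot be an effect of SFTRS. It would nevertheless pass into the difference in mean production losses, and from there into both ratios.

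The Introduction expects SFTRS to lower production losses. A lower employed share in the southern region would produce that result with no service effect, and a higher share could hide a real saving.

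None of the stated methods removes this. The bootstrap resamples patients within the groups as recruited, so a systematic regional difference stays in the point estimate. Varying volumes and prices does not change who was employed. Applying the outcome covariates to costs would help only in part. Age and gender carry some of the information on employment, while ISS and number of complications do not measure it. Psychosocial status cannot be assumed to include employment, because the article lists the two separately.

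**Working it through.** **Plan's own figure.** The article gives no figure for employment or for costs per patient. The only planned figure used here is the group size. The FIM difference is 0.15 × 30.2 = 4.53 with SD 9.5, two-sided 5% and 80% power. A t-test calculation gives 70.01, rounded up to the stated 71 per group. Then 71 × 1.15 = 81.65, rounded up to the stated 82.

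**Step 1: false difference in production losses.** Let pS and pC be the shares employed before trauma in SFTRS and CTCS, and L the mean own production loss per employed patient. L is taken as equal in both groups, which means no service effect. Mean loss per patient is pS × L and pC × L, so

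false difference = (pS − pC) × L; relative to CTCS = (pS − pC) / pC.

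**Step 2: effect on total cost.** Let s be the share of CTCS mean societal cost made up by patients' own production losses, with all other costs equal. The relative change in total cost is s × (pS − pC) / pC.

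All values of pS, pC and s below are assumptions.

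| pS v pC | Own production losses | Total, s = 30% | Total, s = 50% | Total, s = 80% |
|---|---|---|---|---|
| 55% v 60% | −0.05/0.60 = −8.3% | −2.5% | −4.2% | −6.7% |
| 50% v 60% | −0.10/0.60 = −16.7% | −5.0% | −8.3% | −13.3% |
| 45% v 60% | −0.15/0.60 = −25.0% | −7.5% | −12.5% | −20.0% |

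The sign can reverse: 60% v 50% gives +0.10/0.50 = +20% in production losses.

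The upper value of s comes from the Introduction: "Production losses due to acute trauma are estimated at 4 billion Euro", against 1 billion Euro of direct medical costs, so 4 / (4 + 1) = 80%. That is a national ratio for accidents, and it leaves out patient and family costs. It serves only as the top of the range.

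**Step 3: chance imbalance.** With no true regional difference, 82 per group and an assumed employed share of 60%, the SE of the difference in shares is √(2 × 0.6 × 0.4 / 82) = 0.0765. The 95% half-width is 1.96 × 0.0765 = 0.150, or 15 percentage points. This is sampling error and adds no bias.

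**Step 4: precision.** If employed patients' losses have coefficient of variation CV, the loss variance is p × CV² × L² within the employed plus p(1 − p) × L² due to employment. Employment therefore explains (1 − p) / (CV² + 1 − p) of the variance. At p = 0.6 this is 0.4/0.65 = 61.5% for an assumed CV of 0.5, and 0.4/1.4 = 28.6% for an assumed CV of 1.0.

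**Step 5: is employment known for everyone?** The article ties recording to rehabilitation-centre admission. Under Conventional multi-trauma care service, later treatment may instead take place in an outpatient clinic, a nursing home or with a GP or physiotherapist. As written, employment could be missing more often in the CTCS group.

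**The case against.** The strongest objection is that the covariate list is stated for the outcome MANCOVAs. The article sets no covariate rule for costs either way, and a condensed article may leave the cost model to a fuller plan. This is right as far as it goes: a reader might infer that the plan excludes employment from the cost analysis, and the article does not say so. The point still stands as a recommendation. The article itself gives case mix between centres as the reason to adjust, names its covariates explicitly, and leaves out a recorded variable that bears directly on a cost it counts.

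Other stronger readings also go too far:

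- **Employment decides whether any production loss can arise.** Caregiver losses are counted too and do not depend on the patient's job. The statement holds only for the patient's own absenteeism and presenteeism.
- **Production losses are the largest component, at 80% of cost.** The ratio describes trauma nationally. This trial enrols hospitalised patients with a rehabilitation indication, so the medical share may be higher. Losses are valued by a modified friction cost method, and the method behind the national figure is not given.
- **Chance imbalance creates a false service effect.** Resampling patients already reproduces this variation in the bootstrap interval. Here adjustment gains precision and removes no bias.
- **The regional mix will create or reverse the result.** No employed share is given for either region, so a bias is possible but not shown.

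Age may also capture more than one might suppose, because eligibility starts at 18 with no upper limit and patients past working age can enter. That would reduce the gap if age were used for costs, but it would not separate employed from non-employed patients of working age.

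**Conclusion.** The point holds in conditional form. Any true regional difference in pre-trauma employment would enter the incremental societal cost as an apparent effect of SFTRS, and no stated method would remove it. With equal loss per employed patient, a 10-point gap (50% v 60%) moves patients' own production losses by 16.7%. It moves total cost by about 5%, 8% or 13% at production-loss shares of 30%, 50% or 80%.

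The employed shares and the production-loss shares are assumptions, so the actual size and direction are unknown. The finding concerns the societal cost answer and both ratios. It does not touch the FIM and SF-36 comparisons. It should be corrected because the variable is already meant to be collected and the remedy is cheap.

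**What to change.** 1. Record pre-trauma employment (paid work yes/no, hours) at baseline for every patient in both regions, whether or not they enter a rehabilitation centre. The baseline PRODISQ contact is a suitable occasion. The article does not show the questionnaire's content, so add the item if it is not already there.
2. Include employment, together with the case-mix variables already named, as a covariate when estimating incremental production losses and incremental societal costs.
3. Repeat the adjustment inside each bootstrap sample, so that the uncertainty around the ratios refers to the adjusted difference.
4. Report production losses among patients employed before the trauma as a supporting result, and show the employed share by group.

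The cost is one baseline item for all patients and the need to explain an adjusted rather than a raw cost difference. No extra patients or visits are needed.
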